### School-based parasitological surveys

#### Selection of participants

The annual school-based cross sectional survey will be conducted in the main public primary school of each shehia. If a shehia has several public primary schools, the school with most students will be surveyed. If a shehia has no public primary school, no school will be surveyed. In each of the schools, a total of 175 students aged 4–17 years will be randomly selected for urine collection. For this purpose, one class of each nursery and standard 1–6 grades, will be selected based on computer-randomised lists. In the selected classes, all children will line up, stratified by sex. Subsequently, we will systematically select each third child in the lines to be included in the study until 25 children per class are reached. This procedure will be continued until we reach a total of 175 selected children from the 7 selected grades. Accounting for a 20% drop-out due to non-consenting parents, absenteeism of children or inability to produce a urine sample of sufficient volume, we aim for a final sample size of 20 children per standard (i.e. a total of 140 students per school).

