#### Data collection

Each selected child will be provided with an ICF for their parents to read and sign. Each selected child aged 12 years or older will additionally be invited to sign an assent form on its own behalf. On the following day, once signed ICFs and assent forms are submitted, children will be registered, including information about their age, sex, travel history and participation in the last round of MDA. Subsequently, children will be handed over a plastic container labelled with a unique identifier code and invited to produce their own urine sample, which will be collected by the study team on the same morning. In addition, participants from grade 3, 4, and 5 will be invited to participate in a questionnaire interview about the knowledge, attitudes and practices regarding schistosomiasis transmission and prevention (KAP). The children will be asked about their knowledge of the animals that are part of the *S. haematobium* lifecycle, their own water contact behaviour, access to safe water sources, and their knowledge about opportunities to prevent both getting and spreading schistosomiasis.

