### Interventions and data collection

In the study, specific intervention packages will be tailored and adapted to the local micro-epidemiology of urogenital schistosomiasis in the shehias. Low-prevalence IUs will receive tailored surveillance-response measures, consisting of active, passive and reactive case finding, treatment of *S. haematobium*-positive individuals and focal snail control. Hotspot IUs will receive a multi-disciplinary intervention package including MDA, snail control and behaviour change communication. The classification of the study shehias into low-prevalence or hotspot IUs will be based on the results of annual cross-section surveys. Initially, a shehia will be considered a low-prevalence IU if it shows an apparent *S. haematobium* prevalence < 2% in the community-based survey and an apparent *S. haematobium* prevalence < 3% in the school-based survey, based on single urine filtration microscopy. Otherwise, the shehia will be considered a “hotspot” IU (Fig. 3). Results gained over the study period will show whether these thresholds and respective intervention packages successfully sustain and accelerate the gains and prevent recrudescence of *S. haematobium* transmission in low-prevalence IUs. The thresholds will be evaluated annually in light of the results of the cross-sectional surveys and adapted if needed.

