Behaviour change communication and community engagement is key for the success and sustainability of interventions for schistosomiasis elimination [11]. To achieve a change in behaviour, health communication, which takes local knowledge, attitudes and practices into account and integrates the communities in priority settings for decision making and planning of schistosomiasis interventions, is essential [55]. In the hotspot IUs, we will implement behavioural interventions, which were created in a human centred design approach and successfully applied in previous studies in Zanzibar [48, 56–58]. The following intervention components will be implemented: i) installation of washing platforms at a place identified together with the community in close proximity to a clean water source (i.e. pump, tap or well) to provide access and safe alternatives to washing clothes at natural water bodies; ii) training of school and madrassa teachers in classroom-based participatory teaching methods to educate children about schistosomiasis transmission and prevention using flip-charts, snail boards, blood fluke pictures, life cycle drawing, and alternative safe play methods; and iii) school-based health communication days for schistosomiasis prevention, introducing safe play methods with health education components in schools in collaboration with health teachers and classes. Within the annual cross-sectional community- and school-based surveys, we will collect KAP data including information about the perception of schistosomiasis, use of washing platforms and alternative play options, and a potential change in behaviour to assess the impact of the behaviour change and communication measures.

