The impact of behaviour change interventions in schools will be evaluated by assessing knowledge, attitude and practices of schoolchildren over time based on questionnaires.

The impact of the intervention approaches on the *S. haematobium* prevalence will be analysed descriptively.

The diagnostic accuracy of new PoC tests will be calculated by determining the proportion of individuals that have been correctly identified as *S. haematobium*-infected (sensitivity) and the proportion of individuals that have been correctly identified as negative (specificity) in comparison with the reference test.

The number and location of schools, madrassas, health facilities, and water bodies and the abundance of intermediate host snails of the genus *Bulinus* identified by micro-mapping of the IUs, will be analysed descriptively.

Statistical analyses will be carried out with the statistical software STATA and R.

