Finally, good coverage will be key for the success of our intervention approaches. In the low-prevalence IUs, surveillance-response activities will start in schools and be extended in a snowball system to households of *S. haematobium*-infected individuals and the water bodies they use. In hotspot IUs, MDA will be conducted in communities and target all eligible household members in a shehia. Schools, including not only primary schools, but also nurseries, secondary schools and madrassas, will be used as additional venues for MDA to reach as many children as possible. Snail surveys will be conducted repeatedly and multiple times per year at the HWCSs of all known water bodies in hotspot shehias. If *Bulinus* is detected in a water body, the HWCSs will be sprayed with niclosamide. Behaviour change communication including trainings in interactive teaching methods about schistosomiasis for teachers and their equipment with schistosomiasis teaching material will target all public, private and religious schools in the hotspot shehias. Public outreach days (Kichocho days) will be conducted in at least two schools per shehia and reach not only the majority of teachers and children attending the school but additional visitors from the communities. Striking health education messages and knowledge about the transmission and prevention of schistosomiasis will be transferred. Two laundry platforms per shehia will be constructed in close collaboration with the community near clean water sources to provide the communities with safe options for washing clothes. However, the implementation and coverage of the surveillance-response activities in low-prevalence IUs and the intervention package in hotspot IUs will be limited by time, costs and logistical feasibility and require careful and adaptive planning and implementation throughout the study period.

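### Behaviour-change impact in schools is to be judged by KAP change over time with no comparator, although the same interview is collected yearly in low-prevalence schools that do not receive the package

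*Protocol article*

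**What the plan says.** **Analysis.** The Protocol article, under Statistical methods, states: "The impact of behaviour change interventions in schools will be evaluated by assessing knowledge, attitude and practices of schoolchildren over time based on questionnaires". It names no comparison group. The section on hotspot intervention packages says that KAP data from the annual surveys are collected "to assess the impact of the behaviour change and communication measures". Primary and secondary objectives lists the impact of the hotspot interventions among the secondary analyses.

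**Delivery.** Behaviour change is a hotspot measure. Interventions and data collection says: "Hotspot IUs will receive a multi-disciplinary intervention package including MDA, snail control and behaviour change communication". The hotspot section says: "In the hotspot IUs, we will implement behavioural interventions". According to the Discussion, teacher training and teaching material "will target all public, private and religious schools in the hotspot shehias". The other stratum is described differently: "Low-prevalence IUs will receive tailored surveillance-response measures, consisting of active, passive and reactive case finding", plus treatment of positives and focal snail control. Behaviour change is not in that list.

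**Measurement.** The annual school survey "will be conducted in the main public primary school of each shehia". Within it, "participants from grade 3, 4, and 5 will be invited to participate in a questionnaire interview about the knowledge, attitudes and practices". Neither statement is limited to hotspot schools.

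**The concern.** A change in KAP over several years has at least two components: what the package did, and what would have happened anyway. Other health messages, programme activity and repeated study contact in schools can all move KAP answers. A series of hotspot results over time gives only the sum of the two.

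The plan uses the word impact for this result and attaches it to a secondary objective. If KAP rises in hotspot schools, the analysis as stated offers no means of saying how much is due to the package. The avoidable part is that concurrent KAP data from schools outside the package are already being collected.

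Exposure also needs defining. Shehias are reclassified each year on survey prevalence. Trained teachers, teaching material and washing platforms would plausibly outlast a change of class. A contrast by current class could therefore count exposed schools as unexposed.

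**Working it through.** **Inputs from the Protocol article**
- 175 pupils selected per school, 20% drop-out, 20 per grade over 7 grades (Selection of participants, school survey).
- KAP interview in grades 3, 4 and 5 (Data collection, school survey).
- 15 low-prevalence shehias of 20, hence about 5 hotspots (Sample size; a planning figure).
- A shehia without a public primary school has no school survey, so 15 comparison schools is an upper bound.

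**Plan's own figures.** 175 × (1 − 0.20) = 140 = 7 × 20 per school, and 20 × (140 + 250) = 7800 per year. Both reproduce.

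**KAP interviews per year.** 3 × 20 = 60 per school. Hotspot: 5 × 60 = 300. Low-prevalence: at most 15 × 60 = 900.

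**What each analysis estimates**
- Change over time in hotspot schools = package effect + hotspot drift.
- Difference in changes = package effect + (hotspot drift − low-prevalence drift). Drift common to both groups cancels.

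**Precision and false attribution.** Assumed, not in the documents: proportion answering correctly p = 0.5, ICC 0 to 0.10, independent samples at two surveys, normal approximation.
- Design effect DE = 1 + 59 × ICC
- SE (over time) = √(2 × 0.25 × DE / 300)
- SE (difference in changes) = √(2 × 0.25 × DE × (1/300 + 1/900))
- Ratio = √(1 + 300/900) = 1.155

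At ICC 0 the SEs are √(0.5/300) = 0.0408 and √(0.5 × 0.004444) = 0.0471. Multiplied by 1.96 they give half-widths of 8.0 and 9.2 points.

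The last column is the chance that the over-time comparison is significant at two-sided 5% when the package does nothing and KAP drifts up by 10 points.

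| ICC | DE | Half-width, over time | Half-width, difference in changes | Significant with no effect |
|---|---|---|---|---|
| 0 | 1.00 | 8.0 | 9.2 | 69% |
| 0.02 | 2.18 | 11.8 | 13.6 | 38% |
| 0.05 | 3.95 | 15.9 | 18.4 | 23% |
| 0.10 | 6.90 | 21.0 | 24.3 | 15% |

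For a drift of 5 points the last column runs from 23% (ICC 0) to 7.5% (ICC 0.10). For 15 points it runs from 96% to 29%.

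**The case against.** The strongest reply is that the sentence in Statistical methods does not exclude a comparison. It does not say hotspot schools only, and one line in a condensed article is compatible with comparing trends between the two types of shehia. The design is declared as repeated cross-sectional surveys, impact on prevalence is to be analysed descriptively, and no KAP test or attribution rule is given.

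Part of this stands. A reader might infer that the plan has ruled out a comparison, or that it will credit every KAP gain to the package; the text says neither. But the article does state its method for an impact claim, and that method contains no comparator. Its Discussion caveat on power concerns prevalence, not KAP.

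The objections to the comparison itself also stand, as limits:
- Hotspot status follows prevalence, not randomisation, so parallel KAP trends are an assumption.
- Active surveillance reaches grades 3–5 in low-prevalence schools, while hotspot children also get mass drug administration (MDA) and snail control. Behaviour change is not isolated.
- The Background says some randomised areas on the islands received behaviour-change measures from 2012 to 2017. Whether any study shehia was among them is not stated.
- Items on washing platforms and alternative play mean little where neither was provided.
- With about 5 exposed schools, a 10-point effect would lie outside the interval half-width only at an ICC close to zero.

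These limit what the comparison can show. They do not make the uncompared series a better measure of impact.

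**Conclusion.** The concern holds in a limited form. As stated, the analysis cannot separate the package from background change in KAP, and concurrent data that would remove shared drift are already in the survey. At equal variance per interview the cost is an interval about 15% wider. The false-attribution figures rest on the assumed proportion, ICC and drift; they show scale and are not predictions.

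Three stronger readings are not supported:
- **That the contrast would be conservative.** Surveillance contact in low-prevalence schools could shrink it, while the other hotspot interventions could inflate it. The net direction is unknown.
- **That 900 unexposed interviews are assured each year.** This is a ceiling that rests on a planning split of shehias, and classes may change yearly.
- **That repeat interviewing of the same children drives drift.** Classes are drawn at random and every third child is taken. Enrolment is not given, so the re-interview rate is unknown.

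The point affects one secondary objective. It does not touch the primary outcome, the sample size or any decision rule.

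**What to change.** Amend the KAP sentence in Statistical methods as follows.

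1. For items common to all schools (knowledge, attitudes, water contact), report change from baseline in schools that have received the package, alongside the concurrent change in schools that have not yet received it during the study, and report the difference between the two. Allow for clustering by school.
2. Count a school as exposed from first receipt onwards, even if its shehia is later reclassified.
3. Report items on washing platforms and alternative play descriptively, in hotspot schools only.
4. State that the comparison is non-randomised, assumes parallel trends, may be biased in either direction for the reasons listed above, and rests on about 5 exposed and at most about 15 comparison schools, so intervals will be wide.
5. If the comparison is not made, describe the hotspot KAP trend without calling it impact.

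The cost is analysis wording, plus a record of when each school first received the package. No new survey data are needed.

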## Discussion

In the new WHO Roadmap on NTDs published in 2021, the global elimination of schistosomiasis as a public health problem and the validated absence of infections in humans in 25 among 78 endemic countries is set as target for 2030 [5]. To achieve these goals, countries and their schistosomiasis programme managers will need clear guidance on which intervention strategies to apply, which population groups to target, which diagnostics to use, and at what thresholds to change and adapt their strategies [11–13]. In Zanzibar, which is committed to eliminate urogenital schistosomiasis in the next years, a long-term study conducted from 2012 to 2020, revealed considerable temporal and spatial heterogeneity of *S. haematobium* infections that will need to be considered in future intervention planning [6, 17, 18]. Within the SchistoBreak study we will address the focality and heterogeneity of *S. haematobium* transmission in Pemba and aim to investigate novel adaptive intervention strategies as well as standard and new diagnostic tools for schistosomiasis elimination in Zanzibar.

Working in an elimination setting, however, there are foreseeable challenges for analyses and implementation:

First, most of the population in our study area is free of schistosomiasis and there will only be very few *S. haematobium* infected individuals. Hence, even with a very large sample size involving several thousand participants, the study is underpowered and we will most likely not be able to determine the impact of our interventions in terms of statistically significant differences in the *S. haematobium* prevalence assessed in annual cross-sectional surveys. Therefore, as a computable and meaningful primary outcome, we will assess the sensitivity of the surveillance approach, based on the number of *S. haematobium* cases detected by active, reactive and passive surveillance in schools and communities divided by the total number of infected persons estimated from the cross-sectional surveys.

Second, the urine filtration and reagent strip methods that we will apply for the standard diagnosis of *S. haematobium* infection markers are not very sensitively and specifically detecting light intensity infections as primarily found in Zanzibar [29–31, 61]. Hence, in cross-sectional surveys, as well as in the surveillance-response approach, we will likely miss a considerable number of *S. haematobium-*positive individuals and underestimate the “true” prevalence. Clearly, our surveillance system will only be as good as the diagnostic methods employed. The undetected false-negative cases missed due to low test sensitivity might act as a reservoir for infections and contribute to continuous transmission. The false-positive individuals indicated by low test specificity will be chased for nothing and valuable resources and time will be wasted [13]. To improve the surveillance and get a more realistic picture of the “true” prevalence in cross-sectional surveys, in addition to the standard methods, we will apply DNA-based or antigen-based diagnostic tests, at least for the examination of urine samples at baseline and endline and, once readily available and validated, at the PoC during surveillance.

Third, to control the morbidity due to schistosomiasis, WHO provides several thresholds based on the baseline prevalence among school-aged children to decide upon the treatment strategy and frequency of MDA [3, 4]. However, to our knowledge, with regard to the schistosomiasis elimination goals, official thresholds indicating when to increase the frequency of MDA, or stop large-scale MDA and change tactics to surveillance strategies for detecting elimination or resurgence of transmission are not yet published, but urgently needed. These intervention thresholds for elimination settings should ideally be available for or transferable to a set of different diagnostic methods, which, depending on their sensitivity and specificity, will reveal different prevalences in the same population. Cross-diagnostic threshold adaptation has been evaluated for several standard tests used for the identification of both *S. haematobium* and *S. mansoni*, but only for thresholds at 10% prevalence, with samples from school-aged children, and in settings with higher intensity of infections than in Zanzibar [62, 63]. In our study, the thresholds to stratify low-prevalence IUs and hotspot IUs and the implementation of respective intervention approaches are predicated on single urine filtration results in our cross-sectional surveys and an analytical picture of the micro-epidemiology of urogenital schistosomiasis in Zanzibar established over the past 10 years. Due to age-dependent exposure rates [6, 64], we have initially selected thresholds determining hotspot IUs at ≥ 3% prevalence in individuals aged ≥ 4 years sampled in community-based surveys and at ≥ 2% *S. haematobium* prevalence in schoolchildren sampled in school-based surveys. The suggested thresholds will be subject to change and adaptation over the course of the project, i.e. in case we observe a considerable increase of prevalence in the low-prevalence IUs targeted with surveillance response.

Finally, good coverage will be key for the success of our intervention approaches. In the low-prevalence IUs, surveillance-response activities will start in schools and be extended in a snowball system to households of *S. haematobium*-infected individuals and the water bodies they use. In hotspot IUs, MDA will be conducted in communities and target all eligible household members in a shehia. Schools, including not only primary schools, but also nurseries, secondary schools and madrassas, will be used as additional venues for MDA to reach as many children as possible. Snail surveys will be conducted repeatedly and multiple times per year at the HWCSs of all known water bodies in hotspot shehias. If *Bulinus* is detected in a water body, the HWCSs will be sprayed with niclosamide. Behaviour change communication including trainings in interactive teaching methods about schistosomiasis for teachers and their equipment with schistosomiasis teaching material will target all public, private and religious schools in the hotspot shehias. Public outreach days (Kichocho days) will be conducted in at least two schools per shehia and reach not only the majority of teachers and children attending the school but additional visitors from the communities. Striking health education messages and knowledge about the transmission and prevention of schistosomiasis will be transferred. Two laundry platforms per shehia will be constructed in close collaboration with the community near clean water sources to provide the communities with safe options for washing clothes. However, the implementation and coverage of the surveillance-response activities in low-prevalence IUs and the intervention package in hotspot IUs will be limited by time, costs and logistical feasibility and require careful and adaptive planning and implementation throughout the study period.

Despite the highlighted challenges, the SchistoBreak study will fill a critical health knowledge gap and produce important and much needed results. The study will show whether the performance of surveillance-response as intervention in low-prevalence IUs is sufficiently high to detect successfully all urogenital schistosomiasis cases and to respond with adequate interventions so that recrudescence of transmission can be prevented. It will also reveal if the *S. haematobium* prevalence in hotspot IUs can be reduced to very low levels when a comprehensive, multi-disciplinary intervention package is applied. Finally, the study will show whether new diagnostic tests are suitable for application at the PoC and outperforming current standard tests in their sensitivity and specificity to detect *S. haematobium* infections. Hence, our study will shed light on the field applicability and performance of novel adaptive intervention strategies and new diagnostic tools for schistosomiasis elimination and reveal whether progress towards interruption of transmission can indeed be achieved and sustained in the suggested way. The evidence and experiences generated by micro-mapping of *S. haematobium* infections at sub-district community level, micro-targeting of different intervention approaches, and application of novel diagnostic tools can guide future strategic plans for schistosomiasis elimination in Zanzibar and inform other countries aiming for interruption of transmission.

